## **Visit 1 – Week 0**

Consent will be obtained by [name]. EB will complete the eligibility screen, which includes data collection (demographic information, BMI, rehabilitation history, and medical questionnaire including date of last NSAID taken). Subjects will complete the VISA-A questionnaire (a self-report questionnaire which measures Achilles tendinopathy severity). The investigator will use the MyotonPro to assess the transverse tendon stiffness at the location of maximal tendon thickening, and will use the AlgoMed Algometer to assess the subject's pain pressure threshold (PPT) on the most affected area of the Achilles tendon. Testing will be conducted at a controlled rate (30 KPa/s) with the subject lying prone on a treatment plinth. Pressure is gradually applied until the subject first experiences onset of pain, at which point they push a button. In rare cases where the person with CAT has baseline (resting) pain, then they will be instructed to press the button at the first increase in pain.

Subjects will then be issued with either placebo or 10% diclofenac gel. The gel will be supplied by a pharmacist, and the investigator and subject will not know the identity of the tubes. Subjects will be instructed to massage 1 gm of gel on the most painful area of the tendon for 30 - 45 seconds. The subject will also be instructed to how often to apply the gel (every 8 hours/3 times a day for 4 weeks) before the next scheduled appointment. They will be asked to complete a medication administration diary to confirm their compliance with the regimen, to document any medical or paramedical treatments received, and an exercise diary to record their exercise and physical activities.

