### **10.2 Secondary Outcomes**

1. Pain (Numeric Pain Rating Scale, 0 - 10)

- i. Average pain during all tendon loading activities over last week
- ii. Average pain during rehabilitative exercise over last week
- iii. Average pain at rest during last week
- iv. Current resting pain

2. Patient-reported change in symptoms (7 point scale from substantially better to substantially worse)

3. Pressure pain threshold (N) and transverse tendon stiffness (N/m) measured over the site of maximum tendon stiffness

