## **Visit 2**

The second appointment will be scheduled 4 weeks following the initial appointment (within a 5 day margin of error). At the start of the second visit, subjects will be asked which treatment they thought they received, any remaining gel and the study diaries will be collected from the subject, and the outcome measures will be taken (VISA-A, pain, global improvement, non-protocol treatments, side effects, pain pressure threshold, tendon stiffness, returned to pre-injury activity level with no or minimal pain?).

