## **12. Statistical Considerations and Data Analysis**

The pain pressure threshold measurement will be repeated three times and the two closest measures will be used for analysis. To avoid wind up, we will wait one minute between each measure.

A repeat measures ANOVA will be used to detect the effect of time (0, 4, 12 weeks) or treatment (placebo vs active) on VISA-A score. Paired t-tests will be used to detect changes in pain, pain pressure threshold and tendon stiffness from baseline to 4 weeks. The proportion of individuals who have returned to full activity at the different timepoints will be reported as point estimates with 95% confidence intervals. The global rating of change (Likert scale) will be compared between groups using a Mann Whitney-U test.

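### Section 12 analyses change in NPRS pain from baseline, but the Visit 1 procedures do not list the four pain ratings

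*Protocol*

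**What the plan says.** Protocol Section 10.2 puts "Pain (Numeric Pain Rating Scale, 0 - 10" first among the secondary outcomes. It has four items: pain on tendon loading, pain during rehabilitation exercise and pain at rest, each over the past week, plus resting pain at the moment of asking.

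Section 12 fixes the analysis: "Paired t-tests will be used to detect changes in pain, pain pressure threshold and tendon stiffness from baseline to 4 weeks".

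The Visit 1 (Week 0) text in Section 11 itemises what is done before gel is handed out. The eligibility screen covers "data collection (demographic information, BMI, rehabilitation history, and medical questionnaire including date of last NSAID taken". Next comes the VISA-A: "Subjects will complete the VISA-A questionnaire (a self-report questionnaire which measures Achilles tendinopathy severity". Two device measurements follow: tendon stiffness with the MyotonPro, and pressure pain threshold, for which the investigator "will use the AlgoMed Algometer to assess the subject's pain pressure threshold (PPT) on the most affected area of the Achilles tendon".

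At Visit 2 (4 weeks), "the outcome measures will be taken (VISA-A, pain, global improvement, non-protocol treatments, side effects, pain pressure threshold, tendon stiffness". Here pain is an entry of its own, beside the VISA-A and the pressure pain threshold.

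**The concern.** A paired test on change needs two values per participant. The schedule names the second and not the first. The other two variables in the same Section 12 sentence, pressure pain threshold and stiffness, are both measured at Visit 1, so the gap is specific to the pain ratings.

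This is a matter of data collection, so an analysis plan cannot repair it. Three items ask about the preceding week and the fourth about the present moment; none can be properly obtained after treatment has begun. Anyone enrolled before a correction would have no pain change score, and chance imbalance between the arms in baseline pain could be neither seen nor adjusted for. Pain is close to the trial's rationale: Section 2 argues from analgesic mechanisms, and the secondary aim in the Study Summary is worded in terms of change in pain.

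**Working it through.** **Step 1: look for a Week 0 pain rating anywhere in the Protocol.**

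| Place | What it collects | Pain rating? |
|---|---|---|
| 11.1 Recruitment and Screening | Minimal eligibility, by phone or email | No |
| Visit 1, eligibility screen | Demographics, BMI, rehabilitation history, medical questionnaire | Not listed; the questionnaire's content is not shown |
| Visit 1, self-report | VISA-A | No |
| Visit 1, devices | Stiffness, pressure pain threshold | No |
| Diaries issued at Visit 1 | Gel use, other treatments, exercise and activity | No |
| Check-ins, weeks 1 and 3 | Tolerability, side effects, diary reminder | No |
| Visit 2 | Pain, listed separately | Yes |

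The one mention of resting pain at Visit 1 is "In rare cases where the person with CAT has baseline (resting) pain, then they will be instructed to press the button". That is an instruction for the threshold test and does not record a rating. Because Visit 2 lists pain apart from the VISA-A and the pressure threshold, neither of those can stand in for it.

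**Step 2: consequence for the planned test.** For each item the paired difference is d = (Week 4 rating) - (Week 0 rating). Without a Week 0 rating d is undefined, for all four items. Only a comparison of Week 4 values between the randomised arms remains.

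**Step 3: the plan's own figure.** The Protocol gives no precision figure for pain. Its only calculation is for the VISA-A: difference 15 - 5 = 10, SD 17, two-sided alpha 0.05, power 0.80. By the normal approximation n = 2 × (1.960 + 0.842)² × 17² / 10² = 45.4, rounded up to 46 per group, as stated. The t-distribution gives 46.3, so 47. The VISA-A is collected at Week 0, so this calculation is unaffected.

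**Step 4: precision without a baseline.** Let r be the correlation between baseline and Week 4 pain. The Protocol gives no value; 0.4-0.6 is assumed. Take the variance of the unadjusted Week 4 comparison between arms as 1, with equal variances at the two times.

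- Baseline-adjusted comparison (ANCOVA): 1 - r²
- Comparison of change scores: 2(1 - r)

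| r | Week 4 only | ANCOVA | Change score | Week 4 only ÷ ANCOVA | Week 4 only ÷ change |
|---|---|---|---|---|---|
| 0.4 | 1 | 0.84 | 1.2 | 1.19 | 0.83 |
| 0.5 | 1 | 0.75 | 1.0 | 1.33 | 1.00 |
| 0.6 | 1 | 0.64 | 0.8 | 1.56 | 1.25 |

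Against the adjusted comparison proposed below, the unadjusted one has 1.19-1.56 times the variance. Against a between-arm comparison of change scores, over the same range of r, it runs from somewhat more precise to 25% higher variance.

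**The case against.** The best defence is that the Visit 1 text is not a closed list. The Protocol spreads its procedures over several sections: the three repeats of the pressure threshold appear only in Section 12, and the rule for bilateral disease only in Section 11.4. Section 12 itself presupposes a baseline pain value, so the natural reading is an incomplete description and not a decision to skip the rating. The medical questionnaire and the case report forms are not shown and may contain the items.

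That stands, and it limits the claim. A reader might infer that no participant will have a baseline pain score. The document supports only that none is specified.

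A reader might also infer that the trial stands to lose 16-36% of its effective sample for pain (r² for r of 0.4-0.6). That figure is measured against an ANCOVA which the Protocol does not plan, at a correlation it does not state. It describes what the proposed analysis would gain, and is not a loss from the plan as written.

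Nor would the trial be left without any baseline bearing on pain. The VISA-A, which Section 4 ties to pain and impairment, and the pressure threshold are both taken at Week 0, and a Week 4 comparison of the ratings between randomised arms would be unbiased.

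It can also be said that the covariate adjustment goes beyond the mismatch. That is fair: listing the items is enough to remove the inconsistency, and the adjustment is an improvement that the baseline makes possible at no further cost. What the defence does not remove is that, followed as written, Visit 1 leaves a pre-specified analysis impossible, with no way to recover the data later.

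**Conclusion.** The inconsistency is real. Section 12 requires a baseline pain rating, Visit 1 does not list one, and no other section supplies it. If the schedule is followed as written, the planned paired analysis fails for all four items of the first-listed secondary outcome. The primary outcome, hypothesis and sample size are untouched.

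The size is modest and conditional. An unbiased Week 4 comparison would survive, with 1.19-1.56 times the variance of a baseline-adjusted one. This assumes a correlation of 0.4-0.6 and takes as comparator an analysis that is not in the Protocol. Confidence is high that the text has the gap; whether data would actually be lost depends on forms that are not shown. Should-fix.

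**What to change.** In Section 11, Visit 1, add that participants complete the four pain ratings of Section 10.2 together with the VISA-A, before gel is issued. In Section 12, compare the arms at 4 weeks on each rating with its baseline value as a covariate. The paired t-tests, as worded, test change over time and do not state a comparison of diclofenac with placebo.

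State the recall window for the three past-week items at Week 0. Section 11.1 asks participants to avoid moderate to vigorous activity for the 72 hours before Visit 1, which is 3 of the 7 days recalled, and the Visit 2 text states no such restriction. Participants should know which days the loading and exercise items refer to.

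The cost is four 0-10 questions at a visit that already takes place, about a minute per participant, one line in Visit 1 and one sentence in Section 12. The change needs to be in place before enrolment, because the ratings cannot be obtained afterwards.

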## **Check-ins**

The participants will be contacted twice by phone or email during weeks 1 and 3. The investigator will inquire about tolerability of the treatment and any side-effects, and remind the participant to keep filling out the diaries.

## **Visit 2**

The second appointment will be scheduled 4 weeks following the initial appointment (within a 5 day margin of error). At the start of the second visit, subjects will be asked which treatment they thought they received, any remaining gel and the study diaries will be collected from the subject, and the outcome measures will be taken (VISA-A, pain, global improvement, non-protocol treatments, side effects, pain pressure threshold, tendon stiffness, returned to pre-injury activity level with no or minimal pain?).

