## **10. Study Outcomes**

### **10.1 Primary Outcome**

VISA-A score (0-100) at 4 weeks.

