#### AlgoMed Algometer

The Algometer is a computerized pressure meter used to assess tissue pain perception in muscle pain syndromes. The device is set to a specific pressure (KPa) and placed on the site of maximal Achilles tendon pain. The subject's response to pressure threshold and tolerance tests are then processed by software and graphed on the computer for analysis. The subject will lie face down on a treatment plinth for the PPT measurement. The subject presses a button the moment they first begin to perceive pain, and the test is stopped and the pressure value recorded. The same site will be tested on both occasions.

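### The treatment-guess question comes before the week-4 outcomes at Visit 2 and may prime self-reported answers; it should be asked last

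*Protocol*

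**What the plan says.** The order of events is set out in section 11, under Visit 2. It opens with the guess: "At the start of the second visit, subjects will be asked which treatment they thought they received". The same sentence goes on: "any remaining gel and the study diaries will be collected from the subject, and the outcome measures will be taken (VISA-A, pain, global improvement". After non-protocol treatments and side effects, the list ends with "pain pressure threshold, tendon stiffness, returned to pre-injury activity level with no or minimal pain".

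Four other places bear on the point:

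- Section 10.1 makes the primary outcome "VISA-A score (0-100) at 4 weeks".
- Visit 1 describes VISA-A as "a self-report questionnaire which measures Achilles tendinopathy severity".
- The algometer description in section 11.4 makes the threshold depend on the participant: "The subject presses a button the moment they first begin to perceive pain".
- On blinding, Visit 1 says "the investigator and subject will not know the identity of the tubes".

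Nothing in the protocol places the guess after the outcomes, assigns it to someone other than the assessor, or keeps the answer from the assessor.

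**The concern.** At week 4, every outcome except tendon stiffness depends on the participant's own judgement. Asking for a guess first makes the participant put a belief about allocation into words shortly before giving those judgements, and some may then answer in line with it. The baseline VISA-A is completed before any gel is issued and without a guess, so a priming effect would enter only the follow-up score and pass directly into the change from baseline.

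What is at stake is the primary comparison. If the arms guess differently, for instance because of perceived benefit or local skin effects, the effect of voicing the guess does not cancel between them. A second, weaker route runs through the assessor, who may hear the guess before applying the threshold and stiffness tests.

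**Working it through.** **Step 1: order of events.**

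| Step at Visit 2 | Depends on the participant's judgement? |
|---|---|
| Treatment guess | – |
| Gel and diaries collected | – |
| VISA-A (primary) | Yes, self-report |
| Pain ratings, global change | Yes, self-report |
| Pressure pain threshold | Yes, button press at first pain |
| Tendon stiffness | No, device reading |
| Return to activity | Yes, self-report |

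Only the collection of gel and diaries separates the guess from VISA-A. The 12-week VISA-A also follows the guess, but eight weeks later and by email.

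**Step 2: who hears the guess.** For Visit 1 the protocol says "The investigator will use the MyotonPro to assess the transverse tendon stiffness at the location of maximal tendon thickening", and the investigator also applies the algometer. For Visit 2 it names neither the person who asks the guess nor the person who tests. Exposure of the assessor is therefore possible but not established.

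**Step 3: the plan's own figures, as a scale.** The sample size calculation in section 12 assumes mean improvements of 5 and 15 (SD 17 in each arm), a difference of 10, two-sided alpha 0.05 and power 0.80. The normal approximation gives n = 2 × (1.960 + 0.842)² × 17² / 10² = 45.4, so 46 per group, as stated. (The t-based solution is 46.35.) The standard error of the difference at 46 per group is 17 × √(2/46) = 3.54 points. The point does not depend on the sample size.

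**Step 4: when the order biases the comparison.** Suppose that voicing a guess moves VISA-A by *s* points towards the belief: up after guessing active, down after guessing placebo. If a proportion *p* of an arm guesses active, the mean shift in that arm is *s*(2*p* − 1). The difference between arms is

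2*s*(*p*A − *p*P).

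- If *p*A = *p*P, the bias is zero whatever *s* is.
- With *p*A = 0.80 and *p*P = 0.60, the shifts are +0.6*s* and +0.2*s*: both arms move up, and the difference is 0.4*s*.
- With 0.70 and 0.50, the shifts are +0.4*s* and 0: only one arm moves.

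The arms move in opposite directions only if one mostly guesses active and the other mostly placebo. The model has no category for participants who do not know.

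**Step 5: illustrative size.** The protocol gives neither *s* nor the gap in guesses. I assume *s* = 2 to 4 points and try three gaps. The first two come from the skin-reaction figures in section 11.5: dry skin 9.0% and rash 3.0%, 12% if they do not overlap. Put all 12% in the active arm and let all of them guess active. The gap is 12% × 0.5 = 6 points if they would otherwise have split evenly, and 12 points if all would otherwise have guessed placebo. The third gap, 20 to 30 points, is assumed outright.

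| Gap in guessing active | Spurious difference, 2 × *s* × gap | False-positive rate under no true effect |
|---|---|---|
| 6 points | 0.24 to 0.48 | 5.1% to 5.2% |
| 12 points | 0.48 to 0.96 | 5.2% to 5.8% |
| 20 to 30 points | 0.8 to 2.4 | 5.6% to 10.4% |

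The last column is the two-sided rejection rate for a bias *b*: 1 − Φ(1.96 − *b*/3.54) + Φ(−1.96 − *b*/3.54).

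**The case against.** The strongest reply is that participants hold a belief by week 4 whether or not anyone asks. That belief can colour VISA-A in any order, so only the increment from saying it aloud is due to the sequence. This is correct, and it limits the size of the point. It also weakens the main reason for asking first, which is to keep the guess free of the measurement session: by week 4 the guess already reflects how the tendon has fared, so the present order protects little. A small trade-off remains, since a guess taken last may be slightly coloured by the questionnaires and tests.

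Three further objections stand:

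- A guess is not the allocation, so the blinding described under Visit 1 is not breached.
- Assessor influence is limited in any case. Stiffness comes from a controlled device tap, and the threshold from a controlled rate of pressure ended by the participant. The investigator already asks about tolerability and side effects in weeks 1 and 3, so moving the guess removes only part of any cue.
- The order is a design choice, not a contradiction or an error.

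A reader might infer that priming pushes the arms in opposite directions. Step 4 shows that this does not follow from guesses differing by arm. A reader might also infer that the assessor is primed, but the protocol does not say who asks the guess or who tests at Visit 2.

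**Conclusion.** The point holds as a minor, avoidable risk to the primary outcome. The protocol fixes the guess ahead of VISA-A, the pain ratings, the global change rating and the pressure pain threshold, and nothing in it reverses that order or conceals the answer.

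What can be said is that voicing a belief may prime these answers. The treatment comparison is affected only if guesses differ between arms. The size is unknown. The 0.24 to 2.4 points shown above rest on an assumed shift of 2 to 4 points and on assumed gaps in guessing. The lower gaps use the protocol's skin-reaction figures, but under an assumed split between arms and an assumed effect on guessing. It is tempting to read the upper row as inflation of 8% to 24% of the planned 10-point effect (0.8/10 and 2.4/10). The protocol supports neither input to that range, so it should not be quoted as an estimate. Where perceived benefit drives the guess, the effect would be to exaggerate a difference already present, not to create one.

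**What to change.** Move the treatment-guess question to the end of Visit 2, after VISA-A, the pain ratings, the global change rating, the pressure pain threshold, stiffness and return to activity have all been recorded. Collect it on a form that the assessor does not see until measurement is complete.

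This needs no extra visit, participant or instrument, and it keeps the check on blinding. The cost is the small trade-off already noted, that the guess follows the outcome measures.

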## **Final follow-up**

At 12 weeks from baseline (within a 5 day margin of error), participants will be contacted and the VISA-A administered by email. They will be asked the question about return to activity level again (returned to pre-injury activity level with no or minimal pain?). Subjects who received the placebo will be offered a 4-weeks supply of topical diclofenac.

### **11.3 Coding**

All subject information (questionnaires, medical information, test results) will be coded to protect the identity of each subject. The subjects code ID will consist of a sex designation and two-digit code (e.g. M/F-##). The subject's information will be locked in a secure cabinet at Fortius Sport and Health. The subject's ID code and the subject information kept on computer files will be secured with a password. Co-investigators will be the only people with access to the locked cabinet and computer password.

### **11.4 Research tools used**

For all measurements, in people with bilateral Achilles tendinopathy the worse side will be measured.

#### AlgoMed Algometer

The Algometer is a computerized pressure meter used to assess tissue pain perception in muscle pain syndromes. The device is set to a specific pressure (KPa) and placed on the site of maximal Achilles tendon pain. The subject's response to pressure threshold and tolerance tests are then processed by software and graphed on the computer for analysis. The subject will lie face down on a treatment plinth for the PPT measurement. The subject presses a button the moment they first begin to perceive pain, and the test is stopped and the pressure value recorded. The same site will be tested on both occasions.

#### MyotonPro

The MyotonPro is a hand-held device which imparts a small controlled impact (tap) to the surface of the Achilles tendon – the ensuing vibrations are measured by an accelerometer, and tissue stiffness in the transverse plane (N/m) is derived from this.

### **11.5 Safety Considerations**

#### Topical Diclofenac

Side-effects to diclofenac are rare if administered correctly. A meta-analysis that evaluated the safety profile of topical diclofenac reported that diclofenac has a relatively high topical safety index especially when compared to the intolerance experienced with oral dosing. Dry skin and rash were the most common local skin reactions reported in 9.0% and 3.0% of subjects, respectively, in placebo/diclofenac controlled studies. The dry skin and rash were reported as mild-to-moderate and self-resolving.

